#### Demographics

The following demographic characteristics will be collected: gender, age, marital status, number of children, living arrangements with family members, highest level of educational attainment, economic activity status, utilization of senior citizen centres or senior citizen services, use of community or home care services, and household income in the past month.

### Process evaluation

The process evaluation will be guided by the Reach, Effectiveness, Adoption, Implementation, Maintenance (RE-AIM) framework (94). To assess the quality and participant satisfaction, participants will complete a treatment evaluation inventory and rate their satisfaction with their interventionists.

#### Focus group discussion

A subset of participants will be invited to join the focus group discussions conducted separately for each intervention group within 1 week after completing the intervention. During these discussions, participants will respond to a semi-structured, open-ended questions centered on 4 key areas: (i) their reasons and expectations for participating in the study, (ii) their feelings, favourite or least favourite parts, perceived helpfulness, and challenges related to the intervention content, (iii) any positive or negative impacts experienced from the intervention towards their mental health, thought patterns, and social connections, and (iv) their satisfaction with the intervention content, the interventionist, or suggestions for improvements.

### Planned statistical analysis

Descriptive statistics will be used to summarize baseline characteristics of the participants within each arm. An intention-to-treat approach will be adopted. Missing values will not be replaced because mixed-effects models can accommodate participants with at least one outcome measurement under the assumption that data are missing at random. All analyses will be appropriately accounted for the cluster randomized controlled trial (cRCT) design, recognizing that participants are nested within clusters and outcomes within clusters may be correlated. To assess intervention effects of different arms on primary and secondary outcomes, generalized linear mixed models (GLMM) with random intercepts for clusters, fixed effects for time points (i.e., T0, T1, T2, T3, T4, T5), group (using the control group as the reference), and their interaction terms will be utilized. In addition to GLMM, generalized estimating equations (GEE) with robust standard errors and an exchangeable working correlation structure will be used for sensitivity analysis, with small sample corrections applied as needed to control the rate of type I error. To ensure robustness, results from GLMM and GEE approaches will be compared, with multiple testing corrections such as Bonferroni adjustments applied as appropriate. Sensitivity analyses will include per-protocol and complete case approaches to evaluate the influence of adherence and missing data. Mediation analyses of psychosocial and other potential mediators will employ multilevel modelling techniques suited for clustered data. Statistical significance was defined as *p* < 0.05. All statistical modelling will be conducted using SPSS version 29.0, which provides robust tools for multilevel mixed-effects modelling including GLMM and GEE, with options for controlling cluster effects and covariate adjustment.

For the focus group discussions, all recordings will be transcribed verbatim by a research assistant. Two independent researchers will then conduct a thematic analysis of the transcripts using NVivo version 15 (95). The research team will review and agree on the identified codes, organizing them into main categories and subcategories. These categories may be condensed and reorganized as needed. The team will ensure consistency, reach consensus on the meaning and structure of the categories, and develop a finalized list. Ultimately, a set of categorized themes with supporting verbatim quotes will be produced to highlight the major strengths and limitations of the interventions and to inform improvements for their future implementation.

To evaluate the cost-effectiveness of the multi-level intervention compared to the control group, a trial-based economic evaluation will be conducted. Health outcomes will be measured as quality-adjusted life years (QALYs), calculated using the standard area-under-the-curve method based on individual EQ-5D-5L responses over the study period. Resource utilization will be estimated from the provider’s perspective, and costs for the intervention, outpatient care, emergency department visits, and inpatient care will be calculated using a bottom-up costing approach. The multi-level intervention will be considered dominant if it achieves higher QALYs at a lower cost than the control group. If it results in higher QALYs but also higher costs, the incremental cost-effectiveness ratio (ICER), defined as the difference in cost divided by the difference in QALYs (ΔCost/ΔQALYs), will be calculated. The intervention will be deemed cost-effective if it is dominant or if the ICER falls below the accepted willingness-to-pay threshold. The probability of the intervention to be accepted as cost-effective will be evaluated by probabilistic sensitivity analysis over the uncertainties of all parameters of costs and QALYs as well as variation of willingness-to-pay threshold from zero to 3× gross domestic product per capita in Hong Kong, presented as acceptability curves.

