**Methods:**

This pragmatic, assessor-blinded, 4-arm cluster randomized controlled trial will evaluate a multi-level intervention among 1,344 community-dwelling lonely older adults living in poverty. Participants will be randomized equally to one of the four 6-month intervention groups delivered by trained volunteers: individual-level only, individual- + interpersonal-level, and individual- + interpersonal- + community-level interventions against an education-only control group. Data will be collected at six time points: baseline; 2, 4, and 6 months post baseline; and 12 and 24 months after intervention completion. Primary outcome is assessed by the Revised UCLA Loneliness Scale. Secondary outcomes include De Jong Gierveld Loneliness Scale, symptoms of anxiety and depression, perceived stress, life satisfaction, psychological well-being and sleep quality. Potential mediators will be assessed by mindfulness, self-compassion, emotion regulation, perceived social support, social network characteristics, and neighbourhood collective efficacy and identification. Analyses will follow the intention-to-treat principle, employing linear mixed-effects models, regression, mediation, and cost-effectiveness. Qualitative data collected via focus group discussions will be analysed thematically to gain deeper insight into participants’ experiences and perceptions of the different interventions.

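### The stated primary mixed model has an estate intercept but no participant-level or estate-by-time term, so the group-by-time standard errors are wrong (usually too large) and its missing-at-random argument is weakened

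*Protocol article*

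**What the plan says.** The Abstract sets six assessments per participant: "Data will be collected at six time points: baseline; 2, 4, and 6 months post baseline; and 12 and 24 months after intervention completion". Table 1 and the Measures section confirm that the primary outcome is taken at all six.

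Planned statistical analysis gives the model for primary and secondary outcomes as "generalized linear mixed models (GLMM) with random intercepts for clusters, fixed effects for time points", then "group (using the control group as the reference), and their interaction terms will be utilized". The correlation it acknowledges is that between people in one estate: "recognizing that participants are nested within clusters and outcomes within clusters may be correlated". Correlation between the repeated scores of one person is not mentioned.

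The same section declines imputation: "Missing values will not be replaced because mixed-effects models can accommodate participants with at least one outcome measurement", on the assumption that data are missing at random (MAR). A GEE with robust standard errors and an exchangeable working correlation is the sensitivity analysis, "with small sample corrections applied as needed to control the rate of type I error". Its clustering unit is not stated. The section adds: "Sensitivity analyses will include per-protocol and complete case approaches to evaluate the influence of adherence and missing data".

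**The concern.** The data have three levels (visits within participants within estates), and estate effects may drift between visits. The stated model has one random effect, at estate level. Two consequences matter for the group-by-time terms, which carry the trial's main comparisons.

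- **Standard errors.** An estate intercept that is constant over time cancels from any change from T0. What remains in the model's variance is a residual that wrongly contains the stable differences between people (which inflates the SE) and treats estate-level drift as independent noise between individuals (which deflates it).
- **Missing data.** A likelihood analysis uses a dropout's earlier scores only if the model links them to that person's later ones. Here the only link is the shared estate effect. If dropout depends on a participant's own earlier loneliness, the model does not correct for it. The trial allows for 15% attrition, and T5 falls 24 months after a 6-month intervention.

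**Working it through.** **Inputs from the article.** 32 estates over four equal arms gives 32/4 = 8 per arm; 336 per arm gives 336/8 = 42 per estate (Sampling and two-stage cluster randomization; Sample size estimation). ICC is 0.028. The article gives no SE or SD for these contrasts, so there is no figure of its own to reproduce, and everything below is in units of one total SD.

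**Assumptions, not in the article.** r is the within-person correlation inside an estate, 0.4 to 0.7. CAC (estate autocorrelation) is the share of estate variance that stays constant over visits: 1.0, 0.8 or 0.5, with 0 as the extreme.

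**Variance components.** Estate-by-time: s_ct = 0.028 × (1 − CAC). Participant: s_p = 0.972 × r. Residual: s_e = 0.972 × (1 − r).

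**Formulas** for an arm-versus-control change from T0 to one follow-up, complete data:
- True SE = sqrt{2 × (2 s_ct/8 + 2 s_e/336)}
- SE reported by the stated model = sqrt{4 × (s_ct + s_p + s_e)/336}
- SE with a participant intercept added but no estate-by-time term = sqrt{4 × (s_ct + s_e)/336}
- Actual two-sided type I error = 2 × [1 − Φ(1.96 × model SE/true SE)]

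**Worked case, r = 0.6, CAC = 0.8.** s_ct = 0.0056, s_p = 0.5832, s_e = 0.3888. True SE = sqrt{2 × (0.0014 + 0.002314)} = 0.0862. Stated model = sqrt{4 × 0.9776/336} = 0.1079. Ratio 1.25. With CAC = 1 the ratio reduces to 1/sqrt(1 − r), which is 1.58 at r = 0.6.

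Stated model, SE ratio (type I error):

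| r | CAC 1.0 | CAC 0.8 | CAC 0.5 |
|---|---|---|---|
| 0.4 | 1.29 (1.1%) | 1.09 (3.2%) | 0.92 (7.2%) |
| 0.5 | 1.41 (0.6%) | 1.16 (2.2%) | 0.96 (6.0%) |
| 0.6 | 1.58 (0.2%) | 1.25 (1.4%) | 1.00 (4.9%) |
| 0.7 | 1.83 (0.03%) | 1.36 (0.8%) | 1.06 (3.8%) |

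Simulation agrees. At r = 0.6 and CAC 0.8, with 15.2% attrition unrelated to scores, the stated model's mean SE at T3 was 0.110 against an empirical 0.089, and it rejected in 2.0% of null trials.

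**Cost in power, r = 0.6.** An effect that a correct model detects with 95% power equals (1.96 + 1.645) = 3.605 true SEs. Under the stated model, power is Φ(3.605 − 1.96 × ratio): Φ(0.51) = 69% at CAC 1.0 and Φ(1.15) = about 87.5% at CAC 0.8.

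**Participant intercept alone, CAC 0.8.** Ratios are 0.85, 0.83, 0.80 and 0.75 for r = 0.4 to 0.7, giving type I error of 9.6%, 10.6%, 11.9% and 14.1%. Repairing one omission without the other makes the test anti-conservative.

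**Dropout.** Simulated under the null at r = 0.6 and CAC 0.8, with dropout depending on the participant's previous score in opposite directions in the two arms compared:

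| Log-odds slope | Attrition | T5 bias, stated model | T5 rejection, stated model | T5 bias, full covariance |
|---|---|---|---|---|
| 0 | 15.2% | −0.007 SD | 1.4% | −0.008 SD |
| 0.3 | 15.6% | 0.053 SD | 5.0% | −0.005 SD |
| 0.7 | 17.9% | 0.144 SD | 22.4% | −0.005 SD |

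A separate simulation made 15% dropout depend on the T3 score (slope 1 per SD, correlation 0.6). It gave a T5 bias of 0.076 SD when only controls dropped out selectively and 0.155 SD when the arms differed in direction. Adding a participant intercept cut this to 0.002 SD or less.

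**The case against.** The strongest reply is that the article never says the estate intercept is the only correlation term. A within-participant residual covariance is not a random effect, so listing random intercepts does not formally exclude it; the missing-data sentence shows that repeated outcomes are in view; and covariance structure is often left to an SAP. This softens the point but does not remove it. The section sets out the model's terms and the correlation it recognises, and both stop at the estate.

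Several stronger readings are tempting and not supported:

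- **That the stated model inflates type I error to 10–14%.** As written it does so only at estate autocorrelation 0 (ratio 0.75 to 0.83), meaning an estate's level at one visit tells nothing about the next. At 0.8 the model is conservative, and near 0.5 the two errors roughly cancel.
- **That the MAR argument fails outright.** There is no bias if dropout depends only on arm, time and estate, and it largely cancels under the null if the mechanism is the same in all arms. The article gives one overall attrition figure and nothing that points to opposite-direction dropout.
- **That the primary test runs at 6–7% for want of a small-sample correction.** Those levels (6.0% if the right reference is t with 28 df, 7.0% with 14 df) presuppose a normal reference, and the article states none. What can be said is that the correction is worded for the GEE.
- **That the complete-case analysis, or leaving the T0 means unconstrained, is an error.** The article does not claim that complete-case analysis tests MAR, and T0 as an outcome with group-by-time terms is a valid analysis.

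The GEE comparison is partial protection. If clustered on estate, its robust SEs would be sound. But the unit is not given, it is only a sensitivity analysis, and unweighted GEE does not repair MAR dropout.

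**Conclusion.** The point holds as a deficiency in the stated primary model. Over within-person correlations of 0.4 to 0.7, the group-by-time SE is too large by 29% to 83% if estate effects are constant and by 9% to 36% at estate autocorrelation 0.8. At 0.5 it is within about 8% of the truth either way, by cancellation. The likely harm is intervals that are too wide and lost power; modest anti-conservatism, up to about 7%, needs both correlations to be low.

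The stated ground for not imputing does not hold for this model when dropout depends on a participant's own earlier scores. T4 and T5 contrasts can then be biased if that dependence differs between arms; 0.05 to 0.15 SD at T5 is illustrative.

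The within-person correlation, the estate autocorrelation and the dropout mechanism are assumptions. The cluster numbers and ICC are the article's. Because this model produces the primary result, it should be corrected before outcome data are examined.

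**What to change.** State the primary analysis as a linear mixed model with fixed time, group and group-by-time, and random effects for estate, estate-by-time and participant. An unstructured within-participant residual covariance may replace the participant intercept, provided the estate and estate-by-time effects stay. Both additions are needed together. The MAR justification can then stand, conditional on this model.

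Apply a small-sample degrees-of-freedom correction (Satterthwaite or Kenward–Roger) to this primary model as well as to the GEE.

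Optional improvements, not corrections: constrain the T0 means to be equal across arms, which lowers individual-level variance by the factor (1 + r)/2 relative to a change contrast (0.8, or 20% less, at r = 0.6); and add a delta-adjusted missing-not-at-random analysis alongside the complete-case one.

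The cost is revised wording and slightly more modelling. No new data are needed.

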**Figure 2 fig2:**
[figure not shown]
CONSORT flow diagram.

**Table 1 tab1:** Schedule of enrolment, interventions, and assessments for SPIRIT 2025.

	Study period						
	Enrolment		Post-randomization				Close-out
Timepoint	−*t*_1_	*t* _0_	*t* _1_	*t* _2_	*t* _3_	*t* _4_	*t* _5_
Enrolment							
Eligibility screen	×						
Informed consent	×						
Randomization		×					
Interventions							
First-arm (individual-level only)			×				
Second-arm (individual- + interpersonal-level)			×	×			
Third-arm (individual- + interpersonal- + community-level)			×	×	×		
Fourth-arm (education-only control group)			×	×	×		
Maintenance				×	×		
Assessments							
Primary outcomes							
Revised UCLA Loneliness Scale (59, 60)		×	×	×	×	×	×
Secondary outcomes							
De Jong Gierveld 6-item Loneliness Scale (61, 62)		×	×	×	×	×	×
Pittsburgh Sleep Quality Index (63, 64)		×	×	×	×	×	×
Satisfaction with Life Scale (65, 66)		×	×	×	×	×	×
Activities of daily living (73)		×				×	×
Instructional activities of daily living (74, 75)		×				×	×
Physical Symptoms Inventory (76, 77)		×	×	×	×	×	×
Charlson Comorbidity Index (78)		×				×	×
6-Minute Walking Test (79, 80)		×				×	×
Perceived Stress Scale (67, 68)		×	×	×	×	×	×
Hospital Anxiety and Depression Scale (69, 70)		×	×	×	×	×	×
Hong Kong Montreal Cognitive Assessment (71, 72)		×				×	×
Mediators							
Mindfulness Attention Awareness Scale (81)		×	×	×	×	×	×
Self-Compassion Scale-Short Form (82, 83)		×	×	×	×	×	×
Emotion Regulation Scale-Cognitive Reappraisal subscale (84, 85)		×	×	×	×	×	×
Multidimensional Scale of Perceived Social Support (86, 87)		×	×	×	×	×	×
Lubben Social Network Scale (88, 89)		×	×	×	×	×	×
Neighbourhood Collective Efficacy Scale (90, 91)		×	×	×	×	×	×
Cost-effectiveness							
Quality of Life Measures (92, 93)		×	×	×	×	×	×
Use of healthcare services		×	×	×	×	×	×
Demographics							
Age, gender, number of children, education level		×					
Marital status, living with family members		×				×	×
Economic activity status, house		×	×	×	×	×	×
Usage of senior citizen center or service		×	×	×	×	×	×
Usage of community/Home care services		×	×	×	×	×	×
Household income in the past month		×	×	×	×	×	×

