### Sample size estimation

Based on a previous cluster randomized controlled trial designed to detect a difference between control and intervention groups for a continuous outcome (i.e., UCLA Loneliness Scale), an estimated variance was calculated at a two-tailed 5% level of significance, power of 95%, targeting a 0.087 unit difference on the UCLA Loneliness Scale while maintaining a relative precision of ±3.0% (49–52). Taking into account a 15% attrition rate across 24 months (53), unequal cluster sizes, intervention non-adherence, and potential ICC variability of *ρ* = 0.028, an effective sample size of 1,344 participants will be required, with 336 participants in each arm.

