### Measures

All outcome measures are locally validated and have been selected to capture the primary outcome, secondary outcomes and potential mechanisms of change. All outcome assessments will be conducted face-to-face at the participant’s preferred time and location across baseline (T0), as well as at 2 months (T1), 4 months (T2), and 6 months (T3) from baseline, and at 12 months (T4) and 24 months (T5) after the completion of the intervention. To minimize participant burden, outcome measures are prioritized and staggered across timepoints (see Table 2). All assessments will be administered by experienced, independent interviewers blinded to intervention allocation. All interviewers will undergo rigorous training involving comprehensive familiarization with the measurement tools, clinical vignettes, and on-site practice to achieve and maintain high inter-rater and intra-rater reliability (ICC >0.9) throughout the study.

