#### Primary outcome

Loneliness will be assessed by the 20-item Revised UCLA Loneliness Scale (UCLA-LS) (59, 60), where participants will rate each item based on the frequency they experience feelings of loneliness, using a 4-point Likert scale ranging from 1 = Never to 4 = Always. Total scores range from 20 to 80, with higher scores indicating greater levels of loneliness.

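### The primary model measures each effect as a difference in change from baseline; adjusting for the baseline score would be more precise at little cost

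*Protocol article*

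**What the plan says.** The protocol article, under Planned statistical analysis, names "generalized linear mixed models (GLMM) with random intercepts for clusters" and "fixed effects for time points (i.e., T0, T1, T2, T3, T4, T5), group (using the control group as the reference"), together with the interaction of time and group, for primary and secondary outcomes. T0 is thus a level of the time factor. The group term allows the arms to differ at T0, and the interaction carries the divergence afterwards.

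No baseline score is named as a covariate and no common baseline mean is imposed. Covariate adjustment appears once, as a feature of the software: "with options for controlling cluster effects and covariate adjustment". The GEE, per-protocol and complete-case sensitivity analyses are not described as adjusting for baseline either.

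The baseline score will be available. Under Measures, assessments run "across baseline (T0), as well as at 2 months (T1), 4 months (T2), and 6 months (T3) from baseline" and then twice more after the intervention ends. Table 1 marks the primary scale, "Revised UCLA Loneliness Scale (59, 60"), at T0 and at every later visit.

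**The concern.** In a repeated-measures model with a free group effect at T0, the group-by-time term at a given visit is the arm difference at that visit minus the arm difference at baseline. Under random allocation, a baseline difference between arms predicts only part of the later difference. Subtracting all of it adds noise, and it over-corrects when the arms happen to differ at T0. With 8 estates per arm, such chance differences are to be expected.

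What is at stake is interval width and power. This matters most for the incremental comparisons in the Objectives (second arm against first, third against second). Those differences may be smaller than the differences from control, and a Bonferroni adjustment may also apply to them.

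**Working it through.** **The plan's own figure.** Sample size estimation gives 1,344 participants for a "two-tailed 5% level of significance, power of 95"%, but states neither an SD nor a baseline-to-outcome correlation. The figure therefore cannot be tied to either form of analysis, and the check below compares the two in SD units.

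**Inputs from the protocol**
- 32 estates over four arms: 8 per arm.
- 1,344 / 32 = 42 per estate. With 15% attrition, m = 42 × 0.85 = 35.7.
- ICC = 0.028.

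**Assumed inputs (not in the protocol)**
- Individual baseline-to-follow-up correlation within estates, ρ: 0.5 to 0.7.
- Correlation of the estate effect over time (CAC): 0.5 to 0.8, and 1.0 for fully stable estates.

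**Step 1: variance and correlation of estate means** (total SD = 1)
- Variance = ICC + (1 − ICC)/m = 0.028 + 0.972/35.7 = 0.0552.
- Correlation R = [ICC × CAC + (1 − ICC) × ρ/m] / 0.0552.
- Example, ρ = 0.6 and CAC = 0.8: R = (0.0224 + 0.0163)/0.0552 = 0.701.

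**Step 2: weight given to baseline.** If the baseline difference is subtracted with weight b, the variance of the contrast is proportional to 1 + b² − 2bR.
- b = 1 (change from baseline): 2(1 − R).
- b = R (the minimum): 1 − R².
- Ratio: (1 − R²) / [2(1 − R)] = (1 + R)/2, which is below 1 whenever R < 1.

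**Step 3: cost of estimating the slope.** The between-estate slope has to be estimated. Pooled within arms over 32 estates it has 32 − 4 = 28 degrees of freedom, and the expected variance rises by 1 + 1/(28 − 2) = 1.038. With only the two compared arms (16 estates, 14 degrees of freedom) the factor is 1 + 1/12 = 1.083.

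**Step 4: results**

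| ρ | CAC | R | (1+R)/2 | × 1.038 (32 estates) | × 1.083 (16 estates) |
|---|---|---|---|---|---|
| 0.5 | 0.5 | 0.500 | 0.750 | 0.779 | 0.812 |
| 0.6 | 0.8 | 0.701 | 0.851 | 0.883 | 0.922 |
| 0.7 | 0.8 | 0.751 | 0.875 | 0.909 | 0.948 |
| 0.5 | 1.0 | 0.753 | 0.877 | 0.910 | 0.950 |
| 0.7 | 1.0 | 0.852 | 0.926 | 0.962 | 1.003 |

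With the slope pooled over 32 estates, the variance falls by 9-22% for CAC 0.5 to 0.8 and by 4-9% at CAC 1.0. A simulation of four-arm estate means agreed to within about 0.01 in the ratio.

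**Standard errors in the example** (ρ = 0.6, CAC = 0.8)
- Change: √[(2/8) × 2 × 0.0552 × (1 − 0.701)] = 0.091 SD.
- Adjusted: √[(2/8) × 0.0552 × (1 − 0.701²) × 1.038] = 0.085 SD.

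**Step 5: individual score alone.** The slope on the individual score is driven by the within-estate relation, so b is close to ρ. At ρ = 0.5 and CAC = 1.0, 1 + 0.25 − 2 × 0.5 × 0.753 = 0.497, against 2(1 − 0.753) = 0.494 for change: no gain. Two-arm simulations gave ratios of 0.81-0.89 at CAC 0.8 and 0.98-1.02 at CAC 1.0.

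**The case against.** The strongest reply is that a group-by-time mixed model with baseline among the outcomes is a standard, valid analysis, and that a covariate list usually sits in the SAP. The first part is right. A reader might infer that the planned estimate is biased, or that the baseline data are thrown away. Neither follows: T0 is used, only with too much weight. The second part does not remove the point, because the article states the model structure outright and that structure determines how baseline enters.

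It is also true that the article does not say which contrast estimates the effect. The difference in change is the natural reading of the interaction, but it is a reading.

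A reader might take the familiar individual-level ratio, (1 + r)/2, and claim 15-25% less variance at correlations of 0.5 to 0.7. That does not apply to a contrast between randomised estates. Nor does 12-25%, which treats the slope as known and leaves out stable estates. With a slope from only two arms and CAC 1.0, the gain can vanish.

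Three further points stand:
- Modelling only T1 to T5 drops participants who have a T0 value alone, whereas the plan keeps anyone with at least one measurement.
- Residents are invited after estates are assigned (Sampling and two-stage cluster randomization), so baseline differences may not be pure chance. Neither approach is then clearly better.
- Only cluster random intercepts are named. If the model has no participant-level term, its reported variance for the interaction would ignore within-person correlation: at ρ = 0.5, CAC 1.0 and 286 per arm, 4 × 0.972/286 = 0.0136, against a true 0.0136 × (1 − 0.5) = 0.0068. This is a separate issue, but it means that the standard errors above are sampling standard errors and not those that the stated model would print.

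**Conclusion.** The point holds as a moderate efficiency loss in a valid analysis. Under the assumed correlations, baseline adjustment lowers the variance of an arm contrast by about 9-22% when estate effects are partly stable over time (0.5 to 0.8), and by about 4-9% when they are fully stable. In the example the standard error goes from 0.091 to 0.085 SD.

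These sizes depend on an individual correlation of 0.5 to 0.7, equal estate sizes, one follow-up visit at a time and a slope pooled over all 32 estates. The protocol supplies neither of the two correlations. The documents do not support the further inference that this choice leaves the trial underpowered, because without an SD the stated power cannot be checked under either analysis.

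**What to change.** Before outcome data are seen, pre-specify one model fitted to all four arms:
- UCLA-LS at T1 to T5 as outcomes, with group, visit and group-by-visit.
- Both the individual T0 score and the estate-mean T0 score as covariates. The individual score alone may gain nothing if estate effects are stable.
- The same form for each secondary outcome, with its own baseline, at the visits where it is measured.
- The stated T0 to T5 model kept as a sensitivity analysis, because recruitment follows assignment.

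Fitting all arms together matters: it pools the slope over 32 estates and protects the gain. T0 is already scheduled, so no data collection is added. The cost is a change of wording in the analysis plan and the loss from the primary model of participants with only a T0 value, whom the sensitivity analysis retains.
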